#### **Subgroup analyses**

At the end of the study, subgroup analyses for the primary endpoint will be performed according to SARS-CoV-2 vaccinal status at inclusion and the cumulative dose of antibody received. The interactions

between experimental treatment and vaccinal status as well as the dose of antibody received will be explored and tested

### **Secondary endpoints analysis**

Secondary endpoints include the following:

- Proportion of hospitalisation for progressive COVID-19 symptoms, or death by day 14 after randomisation
- Proportion of hospitalisation for progressive COVID-19 symptoms requiring O2 support, or death by day 14 and 28 after randomisation
- All-cause mortality by day 28, 90 and 180 after randomisation
- Proportion of patients with supplemental oxygen by day 14 and 28 after randomisation
- Proportion of patients with non-invasive ventilation by day 14 and 28 after randomisation
- Proportion of patients with intubation and mechanical ventilation by day 14 and 28 after randomisation
- Change in 10-point WHO Clinical Progression Scale score at 14 and 28 days after randomisation
- Duration of hospital admission censored at 28 days after randomisation (for participants reaching primary endpoint)
- Proportion of patients with admission to ITU by day 14 and 28 after randomisation
- Duration of ITU admission censored at 28 days after randomisation
- Proportion of patients with long COVID-19 symptoms and time to recovery assessed by questionnaire at days 28 and 180 post randomisation
- Health-related quality of life assessed using the EQ-5D-5L at 28 and 180 days after randomisation

Binary outcomes will be analysed using Z-tests or Fisher's exact tests. When appropriate Risk differences will also be provided with their 95% confidence intervals. As a sensitivity analysis, generalized linear mixed models (with logit link) with a random centre effect will be performed. Time-to-event outcomes will be analysed using log-rank tests with sensitivity analyses based on Cox regression models with a random centre effect (results will be expressed as hazard ratios with 95% confidence interval). Finally, quantitative outcomes will be analysed using Student's t-tests or Mann-Whitney tests, as appropriate. Sensitivity analyses will consist in mixed linear regression with a random centre effect (results will be expressed as mean differences with 95% confidence interval).

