**Secondary endpoints include:**

**Efficacy:**

1. Proportion of participants with hospitalisation for progressive COVID-19 symptoms, or death by day 14 after randomisation (stages 4 to 9 of the WHO scale)
2. Proportion of participants with hospitalisation for progressive COVID-19 symptoms requiring O2 support\*, or death by day 14 and 28 after randomisation (stages 5 to 9 of the WHO scale)
3. All-cause mortality by day 28, 90 and 180 after randomisation
4. Proportion of patients with supplemental oxygen by day 14 and 28 after randomisation
5. Proportion of patients with non-invasive ventilation by day 14 and 28 after randomisation
6. Proportion of patients with intubation and mechanical ventilation by day 14 and 28 after randomisation
7. Change in 10-point WHO Clinical Progression Scale score by day 14 and 28 after randomisation (see below)
8. Duration of hospital admission censored at 28 days after randomisation (for participants reaching primary endpoint)
9. Proportion of patients with admission to ITU by day 14 and 28 after randomisation
10. Duration of ITU admission censored at 28 days after randomisation
11. Proportion of patients with long COVID-19 symptoms and time to recovery assessed by questionnaire at days 28 and 180 post randomisation
12. Health-related quality of life assessed using the EQ-5D-5L at 28 and 180 days after randomisation

\* O2 support requirement based on O2 saturation level on room air  $\leq 93\%$  and/or Respiratory Rate  $> 30$

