#### **VI-3. Baseline/ Follow-up**

Baseline and follow-up assessments will be organised on Days 1 pre-treatment, 3, 14, 28, 90 and 180 (Table 3). Patients will complete a patient questionnaire and will be contacted by phone. Participants randomised to standard care, or whose care allows it, will have blood samples taken in a health clinic or at home and any follow-up blood, respiratory or saliva samples will be self-sampled or performed by a care nurse.

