| Oxygenation                                          |                                             |                |                | X              | X              | X                                                      |             |                |
| Clinical Progression Scale                           |                                             | X              | X              | X              | X              | X                                                      |             |                |
| QoL and long COVID
Questionnaires                 |                                             | X              |                |                | X              |                                                        |             | X              |
| Adverse event recording                              |                                             | X              | X              | X              | X              | X                                                      | X           | X              |
| Laboratory analyses                           |                                             |                |                |                |                |                                                        |             |                |
| SARS CoV 2 RT-PCR in nose and
throat swabs/saliva | X                             | X              | X  | X  | X  | X                                                      |             | X  |

|                                                                                 |                |                  |                |                |                  |                  |  |                  |
|---------------------------------------------------------------------------------|----------------|------------------|----------------|----------------|------------------|------------------|--|------------------|
| SARS CoV 2 sequencing (whole genome sequencing)                                 | X  | X                |                |                | X    | X    |  | X    |
| SARS CoV 2 isolation from nose and throat swab/saliva (cohort 2 only, optional) |                | X  |                |                | X  | X  |  | X  |

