### **Health-related quality of life**

Health-related quality of life will be assessed using the EQ-5D-5L questionnaire. For health-related quality of life questionnaires, descriptive statistics (n, mean, standard deviation, median, minimum and maximum) will be summarised by time point and treatment group. Actual values and changes over time in scores will also be summarised.

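### EQ-5D-5L is collected on day 1, but the day 28 and day 180 comparisons between arms ignore it and lose precision that the data could give

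*Protocol*

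**What the plan says.** Health-related quality of life is a stated secondary objective (III-2, item 12). The matching endpoint in III-4 is "Health-related quality of life assessed using the EQ-5D-5L at 28 and 180 days after randomisation", that is, the score at each visit and not its change from baseline.

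The row "QoL and long COVID" in Table 3 is marked at baseline (D1), D28 and D180. Section VI-3 places the day 1 assessments before treatment: "Baseline and follow-up assessments will be organised on Days 1 pre-treatment, 3, 14, 28, 90 and 180 (Table 3".

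The general principles in X-3 send all outcomes to simple two-sided tests. The subsection on secondary endpoints lists EQ-5D-5L and then sets the method for quantitative outcomes: "Finally, quantitative outcomes will be analysed using Student's t-tests or Mann-Whitney tests, as appropriate". It continues: "Sensitivity analyses will consist in mixed linear regression with a random centre effect (results will be expressed as mean differences with 95% confidence interval". No baseline covariate is named in either analysis.

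The separate quality-of-life paragraph in X-3 gives descriptive statistics by visit and arm and adds: "Actual values and changes over time in scores will also be summarised". The only mention of prognostic adjustment is in the primary endpoint paragraph, where it is conditional.

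**The concern.** The baseline value of an outcome is often a strong predictor of its later value. Here it is already being collected, but the protocol uses it in no comparison between arms.

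Each cohort is mixed in itself. Cohort 1 combines people aged 70 or over with younger people who have conditions ranging from hypertension to dialysis. Cohort 2 combines transplant recipients, patients with blood cancers or solid tumours, AIDS and primary immune deficiencies. Part of the spread in EQ-5D-5L at day 28 and day 180 is therefore likely to reflect chronic illness that was present on day 1.

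If the day 1 score is left out, that spread stays in the error term and any chance imbalance between arms at baseline stays in the estimate. The confidence interval is then wider than it need be. If the Mann-Whitney option is chosen, the main analysis yields a p-value but no mean difference.

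**Working it through.** **Inputs from the protocol.** 158 patients per group per cohort, raised to 170 for missing data (X-2); 1:1 allocation (VIII-1); two-sided 0.05 (X-4); questionnaire on D1, D28 and D180 (Table 3).

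**Inputs not in the protocol.** The correlation ρ between the day 1 score and the later score, and the size of any EQ-5D-5L difference. Both are assumed. ρ is shown as a range and effects are expressed in SD units.

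**The plan's own figure.** The protocol gives no power or precision for EQ-5D-5L, only the sample size for the primary endpoint. With an unpooled Z-test,

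n = (0.15 × 0.85 + 0.30 × 0.70) × (1.960 + 1.282)² / 0.15² = 157.6, so 158 per group.

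The stated number reproduces. The pooled version gives 161.

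**Variance of the arm difference at a follow-up visit**

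- Unadjusted t-test: 2·SD²/n
- Linear model with the day 1 score as covariate: 2·SD²·(1 − ρ²)/n

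The width of the interval is therefore multiplied by √(1 − ρ²), and the equivalent gain in sample size is 1/(1 − ρ²) − 1. With n = 158, the unadjusted 95% half-width is 1.96 × √(2/158) = 0.221 SD.

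**Power.** Take a difference that the unadjusted test detects with 80% power, so that its ratio to the standard error is 1.960 + 0.842 = 2.802. Adjusted power is Φ(2.802/√(1 − ρ²) − 1.960). At ρ = 0.5: 2.802/0.866 = 3.235; 3.235 − 1.960 = 1.275; Φ = 90%. Because the difference is set by its starting power, the result is the same for 158 and 170 per arm. Only the size of the difference changes: 0.315 SD at 158 and 0.304 SD at 170.

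| ρ (assumed) | Variance factor | Interval width ratio | Equivalent extra patients | Half-width, n = 158 (SD) | Power, from 80% |
|---|---|---|---|---|---|
| 0.2 | 0.96 | 0.98 | 4% | 0.216 | 82% |
| 0.3 | 0.91 | 0.95 | 10% | 0.210 | 84% |
| 0.4 | 0.84 | 0.92 | 19% | 0.202 | 86% |
| 0.5 | 0.75 | 0.87 | 33% | 0.191 | 90% |
| 0.6 | 0.64 | 0.80 | 56% | 0.176 | 94% |
| 0.7 | 0.51 | 0.71 | 96% | 0.157 | 98% |

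Starting from 70% power, the same formula gives 74% at ρ = 0.3, 82% at 0.5 and 87% at 0.6. For a fixed difference of 0.3 SD with 158 per arm, power is 76% unadjusted, against 80% at ρ = 0.3 and 87% at 0.5.

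**Check by simulation.** In 4,000 simulated trials with 158 per arm, the ratio of adjusted to unadjusted standard error was 0.94, 0.87 and 0.72 at ρ = 0.3, 0.5 and 0.7. The formula gives 0.95, 0.87 and 0.71.

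**Change scores are no substitute.** A t-test on change from day 1 has variance factor 2(1 − ρ). This is 1.4 at ρ = 0.3, worse than ignoring baseline, and only equals the plain t-test at ρ = 0.5. The covariate model does better than both at every ρ in the table.

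**The case against.** **Valid as planned.** An unadjusted test in a 1:1 randomised trial is unbiased and keeps its type I error. The endpoint is one of twelve secondary efficacy endpoints, without multiplicity control and declared exploratory. All of this stands. It sets the weight of the point but does not remove it, because an exploratory result is read mainly through its estimate and interval.

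**A matter for the SAP.** The protocol announces a more detailed plan, and the sentence on quantitative outcomes is generic. This has some force for the sensitivity model, where further covariates are not expressly excluded. It has little for the main analysis, because the protocol names the test.

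**Perhaps not tested at all.** The quality-of-life paragraph is purely descriptive, so formal testing of EQ-5D-5L has to be read from the general rule and the list of secondary endpoints. Those two passages do cover it, and on the descriptive reading the day 1 score would still enter no comparison between arms.

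**Small gain.** Every patient is acutely symptomatic on day 1, so ρ may be low, above all for day 180. Deaths and unreturned questionnaires will also reduce the number analysed below 170. Both are fair. The lower rows of ρ in the table may be the realistic ones for day 180. The cohorts are analysed separately, so only the spread within a cohort counts, and the protocol gives no figure for it.

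**Day 1 may not be a clean baseline.** VI-3 makes day 1 pre-treatment, but Table 3 footnote 7 allows randomisation at any time between screening and transfusion, and the trial is open-label. A questionnaire filled in after the arm is known could be affected by it. This stands and has to be part of the fix.

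**Conclusion.** The point holds. The protocol measures EQ-5D-5L on day 1 and fixes main and sensitivity analyses that make no use of it in comparing the arms. The consequence is lost precision, not bias.

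The size depends on a correlation that the protocol does not give. If ρ is about 0.4 or more, the power gain from an 80% starting point is more than 5 percentage points (80% to 86% at 0.4, 90% at 0.5). If ρ is 0.2 to 0.3, the interval narrows by 2% to 5% and the gain is modest. The figures assume a linear model compared with a t-test and do not describe the Mann-Whitney option. Apart from one degree of freedom, adjustment costs no precision, so the direction does not depend on the assumed value.

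This is a desirable change to a secondary, exploratory endpoint. The primary endpoint and its conclusion are not affected.

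**What to change.** In X-3, state that the main analysis of EQ-5D-5L (index and VAS) at day 28 and day 180 is, within each cohort, a linear mixed model of the score on arm and day 1 score, with the random centre effect already planned. Report the adjusted mean difference with its 95% confidence interval and robust standard errors. Keep the unadjusted t-test or Mann-Whitney test as the sensitivity analysis.

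Two rules belong with it:

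- **Timing.** Use as covariate only a day 1 questionnaire completed before the arm is known. In practice, sites should be told to collect it before randomisation.
- **Missing day 1 score.** Keep the patient in the model with a simple rule set in advance, for example mean imputation of the covariate with a missing indicator.

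The cost is a sentence or two in X-3, one covariate in a model already planned, and a site instruction on the order of questionnaire and randomisation. No new data, visits or patients are needed.

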### **Health-related quality of life**

Health-related quality of life will be assessed using the EQ-5D-5L questionnaire. For health-related quality of life questionnaires, descriptive statistics (n, mean, standard deviation, median, minimum and maximum) will be summarised by time point and treatment group. Actual values and changes over time in scores will also be summarised.

### **Safety analysis of intervention**

Safety endpoints include the following:

- Number of serious Adverse Events at 72 hours after randomisation (Grade 3/4 adverse events and AE unexpected for their nature, onset, evolution, severity or frequency)
- Arterial and venous thromboembolic events at 28, 90 and 180 days after randomization

Adverse events and their characteristics will be described using numbers and percentages per treatment arm. The proportion of participants with each of the reported events, as well as the

proportions of participants with at least one SAE will be compared using Fisher's exact tests. The total number of AE/SAEs and SAEs will also be described for each arm, and compared using Poisson models (with a robust error variance if necessary).

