**Safety:**

13. Number of serious Adverse Events at 72 hours after randomisation (Grade 3/4 adverse events and AE unexpected for their nature, onset, evolution, severity or frequency)
14. Arterial and venous thromboembolic events at 28, 90 and 180 days after randomization

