## **VIII. MEASURES TO MINIMISE BIAS**

### **VIII-1. Randomisation**

In addition to receiving usual care, eligible patients will be allocated using a central web-based randomisation service (CleanWeb, Telemedicine Technologies, Boulogne Billancourt, France) available at <https://chrub.tentelemed.com>.

The randomisation service will allocate the treatment based on a pre-specified randomization list generated by the data manager. Separate randomisation lists will be used for each patient population. Randomisation will be performed at a 1:1 ratio, blocked (with randomly varying block sizes of two and four) and stratified by centre. Once randomised, patients are irrevocably enrolled in the study, whether or not they are subsequently found to be eligible or actually receive the allocated treatment. As a consequence, patients should be followed until their last visit, until stopping rules apply or death.

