### **X-3. Statistical analysis**

#### **General principles**

All analyses for reports, presentations and publications will be prepared by the coordinating centre at the Research Methods Unit (uMETH) of the Clinical Investigation Centre, University Hospital of Besançon. A more detailed statistical analysis plan will be developed by the investigators whilst still blind to any analyses of aggregated data on study outcomes by treatment allocation.

Although conducted as a single trial with randomisation stratified on the groups of patients (cohort 1 and 2) for operational and logistical reasons, the findings in each cohort are considered as separate trials and are analysed separately.

The final results will be reported according to the recommendations of CONSORT 2010.

All outcomes will be analysed in superiority (two-sided) analyses using simple hypothesis tests. As sensitivity analyses, generalized linear models will be used to account for stratification on the centre. No correction for multiplicity and no hierarchical testing procedures are planned in analysing secondary outcomes. These analyses will therefore be considered as exploratory in nature.

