#### **X-4. Degree of significance**

All tests will be two-sided, with p values of 0.05 or less denoting statistical significance.

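### The between-arm safety comparison specifies significance tests without effect estimates or confidence intervals, at a size where a non-significant result says little about how much harm is excluded

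*Protocol*

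**What the plan says.** Protocol section X-3, Safety analysis of intervention, begins with description: "Adverse events and their characteristics will be described using numbers and percentages per treatment arm". For comparison, the proportion with each reported event and the "proportions of participants with at least one SAE will be compared using Fisher's exact tests". Total numbers of events are "compared using Poisson models (with a robust error variance if necessary"). No risk difference, rate ratio or confidence interval is named for any safety outcome.

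Two safety endpoints are listed in section III-4: the number of serious adverse events at 72 hours, and "Arterial and venous thromboembolic events at 28, 90 and 180 days after randomization".

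Three other provisions bear on how these comparisons will be read:

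- Section X-4: "All tests will be two-sided, with p values of 0.05 or less denoting statistical significance".
- Section X-3, General principles: "the findings in each cohort are considered as separate trials and are analysed separately". No exception is made for safety.
- Section X-1-3 defines the safety population as the patients who received convalescent plasma.

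For efficacy the protocol does ask for intervals. The primary endpoint has a risk difference with a 95% interval. For binary secondary endpoints, "When appropriate Risk differences will also be provided with their 95% confidence intervals"; the list under that heading does not include the safety endpoints.

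**The concern.** Section IV-1 sets the trial up to evaluate safety as well as efficacy, but its size was chosen for a primary endpoint expected in 30% of controls. Thromboembolic events and severe transfusion reactions may be far less common. For such events, a Fisher test in one cohort will usually be non-significant whether or not plasma adds risk. What a reader of the safety section needs to know is how large an excess the data still allow, and a p-value does not answer that.

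The protocol specifies estimates with intervals for efficacy and none for safety, so it is weakest where the test is least informative. Both cohorts receive the same product, so an estimate combined over cohorts would use more of the randomised data on transfusion harms. The plan mentions no such summary.

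**Working it through.** **Inputs from the protocol.** 158 evaluable per arm, raised to 170 (X-2); maximum 1020 per cohort, so 510 per arm (X-2, interim analysis); "Randomisation will be performed at a 1:1 ratio, blocked" (VIII-1); two-sided 0.05 (X-4); two cohorts analysed separately (X-3). **Assumed:** the control risk of a safety event, because the protocol gives none. The range used is 0.5% to 10%.

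**1. The plan's own figure.** For 30% against 15%, 90% power and two-sided 0.05, the unpooled Z-test formula gives

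n = (1.960 + 1.282)² × (0.30×0.70 + 0.15×0.85) / 0.15² = 157.6, so 158 per arm.

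This reproduces the stated figure. No power or precision is stated for any safety endpoint.

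**2. Exact power of the Fisher test for a doubling of risk.** Power is the sum of the binomial probabilities of all outcomes with more events on plasma and two-sided Fisher p ≤ 0.05.

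| Control vs plasma | 170 per arm (one cohort) | 340 per arm (both cohorts, unstratified) | 510 per arm (one cohort at cap) |
|---|---|---|---|
| 1% vs 2% | 3% | 11% | 18% |
| 2% vs 4% | 10.5% | 26.5% | 41% |
| 5% vs 10% | 34% | 65% | 84% |

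Over the whole assumed range at 170 per arm, the chance of missing a doubling runs from 99.7% (control risk 0.5%) to 31% (control risk 10%).

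**3. A check that needs no control risk.** At 170 per arm, the smallest plasma counts that reach p ≤ 0.05 are 6 against 0 control events, 8 against 1, 10 against 2 and 12 against 3. With 3 control events, plasma would need four times as many before the test flags a difference.

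**4. The Poisson comparison.** For a doubled rate, the Wald test on the log rate ratio has standard error √(1/(n×p) + 1/(n×2p)). At 170 per arm, power is 11%, 18% and 38% for control rates of 1%, 2% and 5%. The fitted model also yields a rate ratio with an interval, but the protocol does not ask for it to be reported.

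**5. What an interval adds.** Take counts close to a true 2% vs 4%.

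- One cohort, 7/170 vs 3/170: Fisher p = 0.34; risk difference +2.4 points (Newcombe 95% CI −1.6 to +6.6); risk ratio 2.3 (score 95% CI 0.67 to 8.2).
- Both cohorts, 14/340 vs 7/340: p = 0.18; risk difference +2.1 points (−0.6 to +4.9); risk ratio 2.0 (0.84 to 4.8).

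Both tests are non-significant. The intervals show that a doubling, and considerably more, is not excluded.

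**6. Gain in precision from combining.** With 2% in each arm, the approximate 95% half-width is 1.96 × √(2×0.02×0.98/n). That is 2.98 points at n = 170 and 2.10 points at n = 340. These are unstratified approximations to a cohort-stratified estimate.

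**The case against.** **This is detail for the statistical analysis plan.** The protocol promises a fuller plan, which is not shown here and may well specify intervals. Fisher and Poisson tests are valid choices, and nothing forbids a combined table. This is why the point is an improvement and not an error. It is still worth raising, because the protocol itself fixes the between-arm safety method and names intervals elsewhere.

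**A reader might infer that p ≤ 0.05 is the only way safety is judged.** The documents do not support that. Counts and percentages are described per arm, the DSMB advises on benefit and risk (IX-4), and the stopping grounds in X-5 include unacceptable risk with no p-value attached. None of these, however, puts a bound on excess risk in the final report.

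**A reader might infer that a non-significant test will be reported as no difference.** The protocol does not say so. It calls the analyses of secondary outcomes exploratory, and the safety endpoints continue the secondary numbering.

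**A reader might take a miss rate of about 90% as a property of the plan.** It holds only for an assumed control risk near 2% at the first-stage size. At 510 per arm and the same risk, it is 59%.

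**Combining does not rescue the test.** This is correct: at 2% vs 4%, power rises only to 26.5%. The gain is in precision and in what is reported.

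**Separate safety analysis is defensible.** This also stands. Section II-5-1 describes transient respiratory worsening seen in immunosuppressed patients, and selection of resistant variants notably in such patients. The documents therefore do not support confining the separate cohort analyses to efficacy.

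**Conclusion.** The point holds as a low-cost improvement to the stated method. The safety section specifies tests without estimates or intervals, applied cohort by cohort. At 170 per arm, these tests have 3%, 10.5% or 34% power to detect a doubling if the control risk is 1%, 2% or 5%. Those control risks are assumptions, and power is higher if a cohort is enlarged. The absence of a named interval is a matter of the text and rests on no assumption.

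Low power for rare harms is usual in a trial sized for efficacy and is not itself a fault of the plan. What can be improved is the reporting: an interval states what excess risk remains possible, and a stratified combined estimate narrows it from about ±3.0 to ±2.1 points at 2% risk. The primary efficacy result is unaffected.

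One conflict must be settled first. As X-1-3 is written, the safety population contains no untransfused control patients, so the between-arm comparison in X-3 cannot be made on it.

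**What to change.** In X-3, Safety analysis of intervention:

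- For thromboembolic events and for having at least one SAE, report the between-arm risk difference with a 95% confidence interval in each cohort (for example Miettinen-Nurminen or Newcombe). Add a supplementary estimate combined over both cohorts and stratified by cohort (for example Mantel-Haenszel).
- For the number of SAEs at 72 hours, which is a count, report the Poisson rate ratio with its 95% confidence interval.
- State that safety p-values are descriptive.

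In X-3, General principles, keep the separate cohort analyses and add only that a combined safety summary will also be given.

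In X-1-3, reconcile the safety population with the between-arm comparison so that control patients are included.

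The cost is a few sentences and some extra table columns, with no new patients and no data beyond those already planned. The small downside is that the combined estimate averages over two populations whose background risks may differ, so it should stand beside the per-cohort results and not replace them.
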